### Participants and recruitment methods

At each of the intervention hospitals, there will be two separate cohorts. The names and contact details of all potential participants will be obtained from an existing hospital database.

*Cohort 1*: (*n* = 10 clinical leaders at each experimental hospital), will be approached by the Hospital General Manager to consider participating in the study. These clinical leaders will be invited to participate via email, which will contain all details about the study, the requirements for participation, and the Participant Information and Consent Form (PICF) (Additional file 1). On the day of the education, cohort 1 will be required to complete the written PICF, Pre-test and Post-test 1 surveys and return them to the researcher who is leading the education program. The PICF will also include consent to participate in a follow up telephone interview. Only those providing their contact details and consent will be contacted to participate in the interviews. Completing the Post-test 2 survey online will imply consent.

*Cohort 2:* (*n =* All nurses and allied health professionals involved in completing falls screening), will be eligible to participate and will be invited to attend a one-hour in-service education program. Staff will be asked to read the PICF (Additional file 2), which outlines the full details of the research project and the requirements for participation. Participants will be drawn from all wards in the five intervention hospitals, excluding paediatric, maternity, emergency and theatre wards. We are aiming for 65% attendance of all nurses and allied health professionals at each experimental site. On the day of the in-service training, cohort 2 will be required to complete the written PICF, Pre-test and Post-test 1 surveys. These will then be returned to the researchers via registered post. The PICF will also include consent to participate in a follow up telephone interview. Only those providing their contact details and consent will be contacted to participate in the interviews. Completing the Post-test 2 survey online will imply consent.

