### Education intervention

#### Cohort 1

Will receive a three-hour education program using best educational design [15], which will educate clinical leaders on the latest evidence on hospital falls risk assessment and guide them in how to implement a new Falls Screening Tool. Teaching methods will include: content delivery on the latest evidence for falls screening; interactive face-to-face teaching; small group critical thinking activities on the challenges of falls prevention in hospitals, and the arguments for and against the use of FRATs; practical exercises using clinical vignettes to compare and contrast the historical FRAT and the new Falls Screening Too; and feedback gauging their views on each of the forms. Participants in cohort 1 will also be provided with the practical skills and associated educational resources, to enable them to deliver an effective, one-hour in-service training session on these topics, to cohort 2.

#### Cohort 2

Will attend a one-hour in-service training and be educated by cohort 1. Methods of educational delivery will also include: interactive face-to face teaching; content delivery on the latest evidence for falls risk assessment; small group critical thinking activities; and practical exercises using clinical vignettes (Fig. 1).

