### Data analysis

*Quantitative data:* Using SPSS, demographic data and responses on all Likert scaled surveys and rating scales, will be analysed descriptively. To see if there is a significant difference between mean scores at Pre-test, Post-test 1 and Post-test 2, where there are three or more mean values to compare together, a one way Analysis of Variance (ANOVA) will be used. Where there are only two mean values to compare, an Independent Samples t-test will be used. Comparisons between groups will be measured according to profession, years of clinical practice, and hospital site. We will determine whether the education intervention resulted in a statistically significant conceptual change to the new form, and whether the education intervention requires further development in terms of content and delivery.

With respect to statistical power and sample size calculations: we are seeking significant differences at the 95% confidence level, so *α* = 0.05. Further, we aim to achieve a statistical power of *π* = 0.8, and to detect effect sizes of Cohen’s *d* = 0.4 and larger. The corresponding sample size required is calculated to be *n* = 50 (using the program *Power and Sample Size v.3.0, 2009*) [25]. Cohort 1 will have the requisite *n* = 50 and Cohort 2 is expected to be at least twice as large as this.

*Qualitative data:* Thematic analysis will be employed to analyse the qualitative data from the semi-structured telephone interviews and the textual responses to open ended questions in the surveys. Themes reflect recurrent and distinctive features of participants’ accounts, characterising particular perceptions and/ or experiences seen as relevant to the research questions [26].

The audio-recorded interviews will be transcribed verbatim in Word and the text transferred into Excel. One researcher will develop initial descriptive codes of the responses to each prompt of the semi-structured interview. A second researcher will check the transcripts, review the initial descriptive codes, and the two researchers will discuss and finalise the framework for analysis. The responses from the focus group participants will be coded using this revised framework and categories identified. Finally, a frequency count for each focussed code will be conducted.

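### The named tests and the Cohort 2 size statement treat clinicians as independent, although Cohort 2 is taught in group sessions by Cohort 1 leaders inside five hospitals

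*Protocol article*

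**What the plan says.** Under Data analysis, the protocol article fixes two tests for mean scores at Pre-test, Post-test 1 and Post-test 2: a one-way ANOVA for three or more means, and an independent-samples t-test for two. Hospital enters only here: "Comparisons between groups will be measured according to profession, years of clinical practice, and hospital site". Session and trainer appear nowhere in the analysis.

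The size statement in the same section uses alpha 0.05, power 0.8 and Cohen's d of "0.4 and larger". It continues "The corresponding sample size required is calculated to be" 50, says that Cohort 1 will have 50, and adds that "Cohort 2 is expected to be at least twice as large as this". It gives no intraclass correlation (ICC) and no design effect.

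The delivery is grouped. Of Cohort 2, the Education intervention section says: "Will attend a one-hour in-service training and be educated by cohort 1". The session includes small-group activities. Participants and recruitment methods puts ten leaders at each hospital, sets a target of 65% attendance at each site, and says of Cohort 2: "Participants will be drawn from all wards in the five intervention hospitals", with some ward types excluded. The Data collection section gives each survey a personal code, so one person's answers can be linked over time.

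**The concern.** Clinicians who share a trainer, a discussion and a local roll-out are likely to change together. Both named tests assume independent observations, and the statement that Cohort 2 is at least twice 50 counts heads as independent units of information. Change in views, behaviour and knowledge makes up the first two primary outcomes. If change is correlated within sessions or hospitals, the p-values for change and the reading of Cohort 2 as comfortably powered may both be wrong.

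The comparison by hospital site is exposed separately. A strong or weak trainer, or an unusual session, can look like a hospital difference, and the article intends to use the results to judge whether content and delivery need further development.

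**Working it through.** **1. The plan's own figure.** Inputs from Data analysis: alpha 0.05 (two-sided assumed, as sidedness is not stated), power 0.80, d = 0.4.

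- One-sample or paired normal formula: n = ((1.960 + 0.842)/0.4)² = 49.06, rounded up to 50. This reproduces the stated figure.
- Independent-samples formula: 99 per group, which does not.

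So 50 is a paired calculation on independent people, with d in standard deviations of the change score and no design effect.

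**2. Effect of clustering on a within-person analysis.** Design effect DE = 1 + (m − 1) × ICC, where ICC is that of the *change* score (stable hospital differences cancel between pre and post). Effective n = n/DE. The true type I error of a nominal 5% paired test is 2 × (1 − Φ(1.96/√DE)). Cohort 2 is taken at its stated minimum, n = 100 in five hospitals, so m = 20 if equal. The document gives no ICC; 0.01 to 0.10 is assumed.

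| ICC of change | DE | Effective n | True type I error | Power at d = 0.4, clustering allowed for |
|---|---|---|---|---|
| 0.01 | 1.19 | 84 | 7% | 0.96 |
| 0.05 | 1.95 | 51 | 16% | 0.82 |
| 0.10 | 2.90 | 34 | 25% | 0.65 |

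Effective n falls below 50 once 19 × ICC exceeds 1, that is, above an ICC of about 0.053. In simulation, the 95% interval from a paired analysis that ignores hospital covered about 92%, 83% and 75% of the time.

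**3. The tests as written.** These also ignore pairing. With pre-post correlation ρ within a person, the ratio of true to naive standard error is √((1 − ρ) × DE). It exceeds 1 (standard error too small) only if (1 − ρ) × DE > 1. The document gives no ρ; 0.3 to 0.7 is assumed.

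| n (per hospital) | ICC | ρ = 0.3 | ρ = 0.5 | ρ = 0.7 |
|---|---|---|---|---|
| 100 (20) | 0.01 | 0.91 | 0.77 | 0.60 |
| 100 (20) | 0.05 | 1.17 | 0.99 | 0.76 |
| 100 (20) | 0.10 | 1.42 | 1.20 | 0.93 |
| 500 (100) | 0.01 | 1.18 | 1.00 | 0.77 |
| 500 (100) | 0.05 | 2.04 | 1.72 | 1.34 |

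At n = 100 and ρ = 0.5, the true type I error of the planned test is about 1%, 5% and 10% across the three ICCs. At n = 500 and ICC 0.05 the ratio is above 1 throughout, and simulated coverage of a nominal 95% interval is about 66% to 85%.

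**4. The hospital-site comparison.** This compares different people, so pairing gives no offset, whether it is made at one time point or on change scores. Five hospitals were simulated with two sessions of 10 in each (assumed) and no true hospital effect. A one-way ANOVA at nominal 5% rejected about 7%, 16% and 30% of the time at session-level ICCs of 0.01, 0.05 and 0.10.

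**5. If the cluster is the session, not the hospital.** With sessions of 10 (assumed) and n = 100, DE is 1.09, 1.45 and 1.90, and effective n is 92, 69 and 53.

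**The case against.** A reader might infer that the planned tests will give standard errors or intervals around change that are too narrow. The document does not support that. It names unpaired tests for people measured repeatedly; with a positive ρ this makes standard errors too large, and at 20 per hospital it can cancel or outweigh the clustering. The 7%, 16% and 25% error rates belong to a paired test, which the article does not plan. It also promises significance tests rather than intervals. This part of the objection stands.

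Nor do the figures show that Cohort 2 is too small. At ICC 0.05 and 20 per hospital, effective n is still about 51. At n = 500 it is about 84: larger hospital groups worsen the naive test's error but do not reduce the information. The 65% attendance target suggests that 100 may be a floor. If hospital differences in change are modelled as fixed, the session-level figures apply, and these stay above 50 across the assumed range.

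The trainer mechanism does not extend to Cohort 1, which the research side teaches. That leaders teach only their own hospital's staff is a fair inference, not a stated fact. Session size and the number of trainers are also not given.

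What the objection does not remove is that the tests and the sizing logic are stated choices that ignore the grouping. Two errors of opposite sign and unknown size do not make a valid test, and the site comparison gains nothing from the offset.

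**Conclusion.** The concern holds in a conditional form. The named ANOVA and t-test, and the size statement for Cohort 2, ignore clustering by session and hospital. For the pre/post tests as written, the direction of the net error depends on the ICC of change, the pre-post correlation and the cluster size, none of which is given. Standard errors will be too small once the analysis is made within-person, and are likely to be too small even for the planned tests if hospital groups are large.

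At 20 per hospital and hospital-level ICCs of 0.01 to 0.10, the within-person cost is a design effect of 1.19 to 2.90. Being at least twice as large as 50 is therefore enough up to an ICC of about 0.05 and not beyond. The site comparison is at risk of false positives whenever session or trainer effects exist. All these sizes rest on assumed ICCs, correlations and equal group sizes.

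**What to change.** - **Record the grouping.** Put hospital and a session/trainer number on each Cohort 2 survey before distribution, and carry them to the online Post-test 2 through the personal code. Session may not be recoverable later from de-identified forms.
- **Replace the named tests** with a repeated-measures mixed model: a random effect for person; fixed effects for time, hospital and hospital-by-time; and, for Cohort 2, a random session/trainer effect with its time interaction. A hospital main effect alone is not enough, because it cancels in pre-post change. Five sites are too few for a reliable random hospital effect, so conclusions then apply to these five hospitals.
- **Test hospital differences against session-level variation.** This needs more than one session/trainer per hospital; otherwise the two cannot be separated and the article should say so.
- **Restate Cohort 2's size** as effective n over a stated ICC range such as 0.01 to 0.10, at the level (session or hospital) that matches the model.

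Adding a cluster correction to the independent-samples test would not be enough, since pairing would still be ignored. The cost is one extra survey field, a few model terms and somewhat wider intervals than a paired analysis that ignores the grouping.

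### The sample size of 50 for 80% power at d = 0.4 fits a paired test, but the plan names an independent-samples t-test, which has about 51% power for Cohort 1's pre/post contrast

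*Protocol article*

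**What the plan says.** All the relevant statements are in the protocol article, mostly under Data analysis.

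- Error rate, power and effect: "we are seeking significant differences at the 95% confidence level, so *α* = 0.05"; "we aim to achieve a statistical power of *π* = 0.8"; and the aim is "to detect effect sizes of Cohen’s *d* = 0.4 and larger".
- Result: "The corresponding sample size required is calculated to be" 50. The section adds that Cohort 1 will have this number and that Cohort 2 should be at least twice as large.
- Tests: mean scores at Pre-test, Post-test 1 and Post-test 2 are compared by one-way ANOVA when there are three or more means. For two, "Where there are only two mean values to compare, an Independent Samples t-test will be used".
- Further comparisons: "Comparisons between groups will be measured according to profession, years of clinical practice, and hospital site".

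No paired or repeated-measures test is named. The section does not say which test the 50 was calculated for, whether testing is two-sided, or which SD standardises d.

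Elsewhere, Participants and recruitment methods gives 10 clinical leaders at each of five hospitals for Cohort 1 (5 × 10 = 50). Data collection has the same people surveyed at three times under a participant code. Strengths and limitations expects loss to follow-up, above all at Post-test 2.

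**The concern.** A sample size belongs to a particular test. A pre/post comparison of the same people uses the spread of their individual changes if it is paired. If it is unpaired, it uses the spread of raw scores at both time points. For the same nominal d, the unpaired formula needs about twice the number per time point. Here the calculation appears to follow the first route and the named analysis the second.

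The primary outcomes are changes in concept, behaviour and knowledge, and the plan will use statistical significance to judge whether conceptual change occurred. If Cohort 1 shows no significant change, a reader will take it as a null result with 80% power. Under the named t-test, the chance of detecting a true raw d of 0.4 is about one in two.

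**Working it through.** **Inputs.** Alpha 0.05, power 0.80, d = 0.4, Cohort 1 n = 50 and Cohort 2 about 100 (at least twice 50) come from the protocol. Two-sided testing is assumed. The pre/post correlation r is not given, so 0.3, 0.5 and 0.7 are used as assumed values.

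**1. Reproduce the plan's figure (paired test, d on the SD of the change).**
n = ((1.960 + 0.842) / 0.4)² = 49.06, so 50. The t-based calculation gives 51.01, and exact power at 50 pairs is 79.2%. The published 50 is reproduced.

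**2. Try the t-test the plan names (independent samples).**
n per group = 2 × ((1.960 + 0.842) / 0.4)² = 98.1, so 99; the t-based answer is 99.08, so 100. Power with 50 per group is 50.8%. One-sided testing does not recover the published figure: it needs 78 per group, and 50 per group gives about 63%.

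**3. Apply the independent test to repeated measures.** The pre and post scores come from the same people, so step 2 does not settle the pre/post case. In raw-SD units:
- Smallest significant difference at 50 per time point: 1.984 × √(2/50) = 1.984 × 0.2 = 0.397.
- The target difference, 0.4, sits almost exactly on that threshold. The observed difference is centred on 0.4 whatever r is, so it passes the threshold about half the time.

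Simulating the independent t-test on correlated pairs confirms this:

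| Assumed r | Power, n = 50 | Type I error, n = 50 | n per time point for 80% power |
|---|---|---|---|
| 0 | 50–51% | 5% | 100 |
| 0.3 | 51% | 2.0% | about 90 |
| 0.5 | 51% | 0.6–0.7% | about 83 |
| 0.7 | 51–52% | below 0.1% | about 75 |

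The type I column follows from the test overstating the variance of the difference by a factor 1/(1 − r). At r = 0.3, the normal approximation is 2 × P(Z > 1.96/√0.7) = 2 × P(Z > 2.34) = 1.9%.

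**4. Paired test on the same data when d = 0.4 is on the raw-score SD.**
d on the change scale = 0.4 / √(2(1 − r)).
- r = 0.3: 0.338, power 65%.
- r = 0.5: 0.400, power 79%.
- r = 0.7: 0.516, power 95%.

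The two definitions of d agree only at r = 0.5.

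**5. Cohort 2.** With 100 at each time point, the independent test has 80% power at r = 0, and about 89% at r = 0.5.

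**6. One-way ANOVA over three time points, treated as independent, 50 each.** Cohen's d does not define a three-mean effect, so a pattern must be assumed. Means of 0, 0.2 and 0.4 SD give 41% power; means of 0, 0.4 and 0.4 give 52%.

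**The case against.** The strongest reply is that the sample size is not wrong. The design is pre/post on the same people, the participant code would allow linkage, and 50 is the right answer for a paired contrast with d on the SD of the change. This stands. The fault lies in the named test and its mismatch with the calculation.

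Three stronger readings are tempting, and the documents do not support them.

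- **That every pre/post contrast needs about 100 per time point.** This holds only for unrelated samples. On repeated measures the independent test needs about 90, 83 or 75 at assumed correlations of 0.3, 0.5 and 0.7. By the same reasoning, the detectable d of 0.57 for 50 v 50 applies only to separate groups.
- **That the whole study is underpowered.** Cohort 2 is expected to be at least about 100, and with full response it would reach 80% or more even unpaired.
- **That the plan claims 80% power for comparisons by profession, years of practice and site.** It lists these comparisons but does not say that 50 people power them. Splitting Cohort 1 as 25 v 25 (28% power at d = 0.4) is only an illustration, since no such split appears in the plan. Likewise, five sites would go to ANOVA, not to a 10 v 10 t-test.

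It can also be said that the mismatch makes the test conservative and so creates no false positives. For positively correlated scores that is correct. It does not repair the power statement, which is what a null result would be read against.

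**Conclusion.** The point holds in a limited form. The stated 80% power for Cohort 1 is not delivered by the t-test the plan names. It is about 51% at a raw d of 0.4 with 50 complete responses per time point, at every correlation tried. The nominal 5% error rate is not delivered either: it is about 2% at r = 0.3 and 0.6–0.7% at r = 0.5. Comparisons of genuinely separate groups need 99 to 100 per group for d = 0.4. Cohort 2's pre/post contrast is not short of power if about 100 respond at both times.

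The 51% rests on two-sided testing (about 63% for one-sided testing of independent samples) and full response. The type I figures and the paired power on the raw-score scale rest on assumed correlations, because the protocol gives none. The ANOVA figures rest on assumed patterns of means.

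The article itself fixes the tests, effect size, sample size and claim that Cohort 1 meets it. The inconsistency is therefore in the text as published, not a detail left to another document.

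**What to change.** 1. Name a paired or repeated-measures analysis (paired t-test, repeated-measures ANOVA or mixed model) for the Pre-test, Post-test 1 and Post-test 2 contrasts, with surveys linked by the participant code described under Data collection.
2. Restate the power along these lines: paired within-cohort contrast, d = 0.4 on the SD of the change, two-sided alpha 0.05, 50 complete pairs, 79% power. Specifying complete pairs matters because 50 is Cohort 1's full size and loss to follow-up is expected.
3. If d is meant on the raw-score SD, show the range under assumed correlations: 65% at 0.3, 79% at 0.5 and 95% at 0.7.
4. State that this figure does not cover the comparisons by profession, years of practice or hospital site.

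Keeping the independent t-test for the pre/post contrast and quoting 51% power is not an acceptable alternative, because that test is miscalibrated on repeated measures.

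The cost is about a paragraph of text and a narrower, less favourable power statement. No extra participants are needed.

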### Strengths and limitations

This study is unique and the educational program can be delivered in a busy, time pressured clinical environment using clinical champions (leaders) and a ‘train the trainer’ approach. We shall clearly report the educational features so that others can adopt a best practice approach to educational design. The education interventions are designed to be readily implemented across other hospital sites and applied to other clinical education interventions. This study is not without limitations. There is a time factor related to educating Cohort 2, and education on a new clinical form may not be seen as a high priority for clinicians in a busy clinical environment with competing demands on time. There is also the potential for inaccurate self-reporting caused by recall bias [30] influenced by different clinicians’ perceptions. Loss to follow up is also likely, particularly for post survey 2 when moving from paper based surveys to online surveys.

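### Cohort 1's n = 50 is the number of leaders approached, with no margin for refusal or loss, so the stated 80% power is not secured at Post-test 2

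*Protocol article*

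**What the plan says.** The protocol article's Data analysis section sets α = 0.05 ("we are seeking significant differences at the 95% confidence level"), power 0.8 and an effect of Cohen's d = 0.4 or larger. It gives the resulting requirement as n = 50 and then says "Cohort 1 will have the requisite" n = 50, with Cohort 2 expected to be at least twice that size. The same section lists Pre-test, Post-test 1 and Post-test 2 as the means to be compared. It names one-way ANOVA for three or more means and an Independent Samples t-test for two.

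Participants and recruitment methods defines Cohort 1 as "10 clinical leaders at each experimental hospital", who "will be approached by the Hospital General Manager to consider participating in the study". The Design section places the study at five intervention hospitals. Taking part requires written consent, and Risk management and safety allows withdrawal at any time. Strengths and limitations adds: "Loss to follow up is also likely, particularly for post survey 2 when moving from paper based surveys to online surveys".

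**The concern.** The number needed and the number approached are the same. The article says Cohort 1 will reach the requirement, yet those 50 people have still to agree, and the article itself expects some of them not to answer the third survey. It states no response or retention assumption and no replacement for leaders who decline.

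Post-test 1 is completed straight after the teaching. Post-test 2, two months after the new tool is introduced, is the only survey wave that can show whether change was retained in practice, and behavioural change is part of the first primary outcome. If readers take 80% power as given there, a non-significant Cohort 1 result could be read as evidence that nothing was retained, when the study may simply have had too few responders.

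**Working it through.** **Inputs from the protocol article.** α = 0.05 (sidedness not stated; two-sided assumed), power 0.80, d = 0.4 and n = 50 (Data analysis); 10 leaders per hospital (Participants and recruitment methods); 5 hospitals (Design). No loss rate is given, so 10% to 50% is assumed below to show a range.

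**Number approached.** 10 × 5 = 50.

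**Reproducing n = 50.**
- Paired, two-sided, normal approximation: n = ((z₀.₉₇₅ + z₀.₈₀)/d)² = (2.8016/0.4)² = 49.06, so 50.
- Paired, exact noncentral t: 51.01, so 52. This is within 2 of the stated figure.
- Paired, one-sided: 39 (normal) or 41 (t). Does not match.
- Independent samples, two-sided: 99 (normal) or 100 (t) per group. Does not match.
- Independent samples, one-sided: 78 per group. Does not match.

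The stated 50 is therefore a paired calculation with dz = 0.4 (mean change divided by the SD of change). It contains no inflation for refusal or loss.

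**Power when fewer than 50 respond (exact paired t, dz = 0.4, two-sided α = 0.05).**

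| Assumed combined refusal and loss | Responders | Power | dz detectable at 80% power |
|---|---|---|---|
| 0% | 50 | 79.2% | 0.40 |
| 10% | 45 | 74.7% | 0.43 |
| 20% | 40 | 69.4% | 0.45 |
| 30% | 35 | 63.3% | 0.49 |
| 40% | 30 | 56.3% | 0.53 |
| 50% | 25 | 48.4% | 0.58 |

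To keep 50 responders at Post-test 2, the number approached would be 50/(1 − loss), rounded up: 56 at 10%, 63 at 20%, 72 at 30%, 100 at 50%.

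**Under the test the article names.** For an Independent Samples t-test at d = 0.4, power is 50.8% with 50 at each of two waves and no loss, and 46.2% for 50 against 40.

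**Dependence on the scale of d.** If d = 0.4 is standardised on raw scores with equal SDs at both waves, dz = d/√(2(1 − r)), where r is the pre-post correlation (values assumed):
- r = 0.5: dz = 0.4/√1.0 = 0.40, as in the table.
- r = 0.6: dz = 0.4/√0.8 = 0.45; power at n = 40 is 79%.
- r = 0.7: dz = 0.4/√0.6 = 0.52; power is 89% at n = 40, 84% at n = 35 and 78% at n = 30.
- r = 0.3: dz = 0.4/√1.4 = 0.34; power is 65% at n = 50 and 55% at n = 40.

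**The case against.** A reader might infer that 80% power will definitely be missing at Post-test 2, or that the article contradicts itself or makes an arithmetic error. The documents do not support these stronger readings.

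- **No arithmetic error.** 10 × 5 is 50, and the required 50 can be reproduced.
- **Disclosure is not contradiction.** Naming likely loss as a limitation is compatible with having a sample-size target. Retention assumptions and replacement rules may also sit in a fuller protocol that is not shown. What remains is the firm wording in the article: it says Cohort 1 will have the number, not that it aims for it.
- **The loss is unquantified.** At 10% loss, power falls only from 79.2% to 74.7%. The figures near 50% need losses for which the article gives no basis.
- **The scale of d matters.** With a raw-score d and r = 0.7, 80% power survives 30% loss. With r below 0.5, it is already out of reach with all 50 responding. So power at Post-test 2 is not secured, but it is not shown to be absent.
- **The named test costs more than attrition.** Under the Independent Samples t-test, power is about 51% before any loss, and moving to 50 against 40 removes only about 5 points more. That is a separate problem. It also means that even Pre-test to Post-test 1, both done on paper the same day, cannot be called powered unless the analysis is paired.

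It could also be said that the power sentence names no wave and so claims nothing about Post-test 2. This does not stand: the same section lists Post-test 2 among the means to be compared and does not exempt it. Reading ten per hospital as an enrolment target does not help either, because 50 enrolled still leaves nothing for the loss expected later.

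**Conclusion.** The point holds, for Cohort 1 only. On the terms that reproduce n = 50 (paired, two-sided, dz = 0.4, everyone responding), 80% is an upper limit with no margin. Any refusal or loss takes power below it, by about 4.5 points at 10% loss and about 10 at 20%. The direction on those terms needs no assumed loss rate; the size does, and it also depends on the pre-post correlation if d refers to raw scores. Cohort 2, expected to number at least 100, could lose half and still have 50 for a paired comparison. This is an overstated claim that should be corrected; it does not invalidate the study.

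**What to change.** In Data analysis:

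1. Replace the statement that Cohort 1 will have the required 50 with one that at most 50 leaders will be invited.
2. State that the 80% figure assumes a paired analysis, dz = 0.4 and all 50 responding (exact power 79%), and that under the Independent Samples t-test now named it would be about 51%.
3. For Post-test 2, give paired power over an assumed loss range: 75% at 10%, 69% at 20%, 63% at 30% and 48% at 50%, with detectable dz of 0.43, 0.45, 0.49 and 0.58. Note that these depend on the pre-post correlation if d is on the raw-score scale.
4. Report the Cohort 1 change to Post-test 2 as an estimate with a 95% CI, so that a non-significant result is not read as no retained change.

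The cost is a text change with no added recruitment. The quoted Post-test 2 power becomes less favourable.
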